### Data Collection

Ethical approvals have been obtained from 3 ethics boards and operational approval obtained at the health regions and cancer agency. Meetings with the site collaborators and data collectors are occurring every month to ensure study progression. Four part time research assistants, who are Registered Nurses and one social worker, were trained in giving instructions for the hope activities as well as consent and data collection procedures. Training included orientation manuals, practice sessions and inter-rater reliability testing.

The primary oncology nurses and social workers at the Cancer Centres and the home care and palliative care nurses in the health regions have been identifying advanced cancer patients based on the inclusion criteria. They are approaching these patients and asking if a RA could talk with them about a study that would involve a family member who is providing care for them. They are asking their permission to approach their caregiver (who meets the inclusion criteria) to determine their willingness to speak with a researcher. If they agree the RAs are contacted. The RAs then contact potential subjects by phone. During the telephone conversation a brief outline of the study will be given and arrangements are made to meet with them in their homes at a convenient time. At the first visit a written informed consent is obtained from the person with advanced cancer and their family caregiver. Throughout the study process consent is used (before each visit the RA will ask if subjects would still like to participate in the study).

Figure 2 outlines the proposed data collection procedure for this study. At the first visit demographic information of the caregiver and family member is being collected, such as length of time care giving. The subject is asked for permission to collect their health services utilization data with their health services number. The RAs then assess the care recipient's functional status by assigning a PPS score. Then baseline caregiver measures of hope, quality of life, self-efficacy and loss and grief are collected. All subjects then receive the LWHP. The instructions are left in the home with the subjects. Supplies such as journals, audio tape recorders, audiotapes and pens are also left with the subjects to use if they wish. A pamphlet is given to all the subjects with general study information and the contact information of the RA if they have questions before the next visit.

**Figure 2 F2:**
[figure not shown]
**Data Collection**.

The second visit is scheduled for 1 week after the first visit. During the second, third, fourth fifth and sixth visit data is collected as per the first visit except for the demographic form. Further, subjects are asked additional questions such as how much time they spent during the week on their hope activity. At the second visit journals are photocopied.

Each visit is about 1-1.5 hours at the maximum to prevent fatigue. A week before each visit a reminder card is mailed to the caregiver's homes. Three days before the scheduled visit the RA's will phone to remind subjects of the data collection visit. To encourage retention birthday cards, a fridge magnet with the Living with Hope Logo and a newsletter is mailed from the team.

The site collaborator is also notifying the RAs as soon as a caregiver becomes bereaved. Data collection is continuing through bereavement following a one month time lapse from the death of the care recipient if subjects have completed the LWHP. In our preliminary work with caregivers who are bereaved data collection has not caused distress. This is supported by another study whose bereaved caregivers reported benefits of participating within the first year following bereavement [25]. Data collection will take place over 28 months.

### Data Analysis

Quantitative data will be cleaned, checking for out of range values, skip pattern problems and duplicates. Data will be entered into SPSS v. 15. Tests of normality will be completed to determine appropriateness of statistical methods. In the case of missing data, regression analysis of subjects with complete data will be used to predict missing data scores. Statistical significance for all analyses will be set at p < .05. To test reliability of all measures in this study, alpha coefficients will be determined. Descriptive analysis of demographic characteristics will be completed to describe the sample and correlation coefficients/chi-square calculated to determine if there are relationships between demographic characteristics and other variables. If there are significant correlations they will be added to the model. The journal writings will be transcribed verbatim by an experienced transcriptionist and checked for accuracy by a RA. Qualitative data will be managed using NVIVO8 software.

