Sample Size: Sample size has been determined based on the requirements of the statistical methods that will be used to test the hypotheses and approximation of subject attrition rates. Path Analysis is the statistical analysis for the main hypothesis of testing the LHWP at week one and two. According to Munro [26] sample size and power calculations for Path Analysis can be made using Cohen's formulation for the most complex regression equation in the Path model. Thus, for a power of 0.80, and an alpha of 0.05, a regression equation, including 6 variables [general self efficacy, loss/grief, hope (factor1), quality of life (mental health sub score), and health services utilization (physician visits and prescriptions)] would require 98 subjects. As the study progresses, caregivers will become bereaved. The exact time and percentage of caregivers who will be bereaved is unknown. Based on Saskatoon Health Region Palliative Home Care data in the year 2001-2002, the average length of stay for palliative patients is 70 days (2.3 months) with 25% dying in 13 days, 50% in 36 days and 75% in 82.75 days. This means that approximately 50% of the subjects may become bereaved in a little over a month. In order to have sufficient numbers of subjects in both groups (active and bereaved caregivers) the sample size will be doubled to 200. Two hundred subjects would provide adequate power for the proposed analysis, so sampling will continue until this is achieved.

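### Filling missing scores with regression predictions and testing them as observed understates standard errors and inflates type I error of the path coefficients

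*Protocol article*

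**What the plan says.** The protocol article has one missing-data rule, in Data Analysis: "In the case of missing data, regression analysis of subjects with complete data will be used to predict missing data scores". It covers all quantitative scores and makes no exception by visit, aim or bereavement. The same paragraph adds: "Statistical significance for all analyses will be set at p < .05".

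The main hypothesis (Specific Aim #1) is tested by path analysis, described as a series of multiple regressions, on change scores at 1 and 2 weeks. Under Sample Size the article reasons that "sample size and power calculations for Path Analysis can be made using Cohen's formulation for the most complex regression equation in the Path model" and continues: "Thus, for a power of 0.80, and an alpha of 0.05, a regression equation, including 6 variables" "would require 98 subjects". To have enough active and bereaved caregivers, "the sample size will be doubled to 200".

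On bereavement, Sample Size cites one region's palliative home care data, "with 25% dying in 13 days, 50% in 36 days and 75% in 82.75 days", and calls the exact timing and percentage in this study unknown. Data Collection (text after Figure 2) says: "Data collection is continuing through bereavement following a one month time lapse from the death of the care recipient if subjects have completed the LWHP".

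**The concern.** A score replaced by its regression prediction lies exactly on the fitted surface. It contributes no residual, yet it counts as a full observation. Because the main analysis is itself a set of regressions, the residual variance is understated, the effective sample size is overstated, and p-values are too small. The claim at stake is the central one: that self-efficacy and loss/grief predict changes in hope and mental-health quality of life. The same understated errors would carry into the Aim 3 repeated-measures analysis.

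A second issue concerns who is missing. Aim 1 is tested at weeks 1 and 2, and collection pauses for a month after a death. A caregiver bereaved before one of those visits has no score there, so the complete subjects used for prediction are still active caregivers. If bereaved caregivers are nevertheless kept in Aim 1, the rule can supply them only with scores typical of active caregivers.

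**Working it through.** **1. The plan's own figure.** For an overall F test with u = 6 predictors, alpha 0.05 and noncentrality f² × N, an assumed medium effect f² = 0.15 (the article states none) gives power 0.798 at N = 97 and 0.804 at N = 98. The stated 98 is reproduced.

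**2. Only the outcome missing, predicted from the model's own variables.** Inputs: n = 200 (Sample Size); k = 6 predictors, taken from the six variables listed there; missing share 10% or 25%, assumed because none is given; missing completely at random. Refitting after imputation leaves the slopes and the residual sum of squares unchanged. Only the divisor and the apparent number of subjects grow, so the ratio of reported to correct standard error is approximately

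r = √[ (n_obs − k − 1)/(n − k − 1) × n_obs/n ].

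- 10% missing (n_obs = 180): r = √(173/193 × 180/200) = 0.898.
- 25% missing (n_obs = 150): r = √(143/193 × 150/200) = 0.746.

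The nominal cut-off is t = 1.972 on 193 degrees of freedom. On the correct scale it becomes 0.898 × 1.972 = 1.77 or 0.746 × 1.972 = 1.47. The two-sided tail areas (173 and 143 degrees of freedom) are 7.8% and 14.4%. Simulation with 4,000 replicates gave 7.5% and 14.3%, with standard-error ratios of 0.897 and 0.742. With k = 2 the formula gives 7.8% and 14.2%, so the number of predictors hardly matters for one coefficient.

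**3. Whole visit missing, all week-2 scores predicted from baseline.** The post-baseline mediators are then missing too and cannot serve as predictors. Simulation: n = 200, change in hope regressed on changes in self-efficacy and grief, no true relation, uncorrelated baselines, baseline-to-week-2 correlation assumed 0.5 to 0.7.

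| Missing | Type I error, one coefficient: outcome only | Type I error, one coefficient: whole visit | Observed cases only |
|---|---|---|---|
| 10% | 7.5-8% | 6-7% | about 5% |
| 25% | about 14% | 10-12% | about 5% |

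A joint F test of several paths is affected more. With six predictors and only the outcome missing it rejects 11.6% and 32.0% of the time. With the whole visit missing, and two predictors, it rejects 7.6% and 12.9%.

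**4. R-squared.** In the outcome-only case the explained sum of squares grows by about g = n/n_obs while the residual sum stays fixed, so R²_imp ≈ gR²/(gR² + 1 − R²). At 25% missing and f² = 0.15, the observed-case mean is 0.164, which gives 0.2187/(0.2187 + 0.836) = 0.207; simulation also gave 0.207. In the whole-visit case under the null it moved only from 0.014 to 0.015 at 25% missing. With baselines correlated at 0.4 the rise was at most about 0.01.

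**5. Bereavement text side by side.**
- Purpose: bereaved caregivers are retained if possible.
- Specific Aim #1: lists the RGEI or its non-death version at 1 and 2 weeks; Table 1 assigns the RGEI to bereaved caregivers.
- Data Collection: nothing is collected for a month after the death, and collection continues only for those who completed the two-week program.
- Data Analysis: missing scores are predicted, without exception.

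The first two suggest that bereaved caregivers belong in Aim 1 at weeks 1 and 2. The third means they cannot be measured there. The fourth, read literally, would fill the gap. The four must be reconciled.

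**6. Power without the rule.** At f² = 0.15, 150 informative subjects give 95.7% power, against 99.2% with 200.

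**The case against.** The article is condensed, and it does not say in words that imputation is done once or that imputed scores are treated as observed. That is fair, but it is the plain reading of a sentence that names a method and adds nothing about uncertainty. Adding a single random residual would not rescue it: one-coefficient type I error at 25% missing was still 12.2%.

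No missing-score rate is given. The 25% dying within 13 days describes one region's palliative home care in 2001-2002, while this study also recruits from ambulatory cancer clinics. This stands. If few scores are missing, the inflation is modest.

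Two stronger readings are tempting. A reader might infer that the rule always makes the model appear to explain more variance than it does. That holds when an isolated outcome is predicted from the model's own variables, but nearly vanishes when a whole visit is lost, which is the pattern early bereavement would produce. A reader might also infer that about a quarter of subjects, newly bereaved, will be given active-caregiver scores. The documents do not establish this. Someone bereaved by day 13 has not completed two weeks of journaling, and collection continues only for those who have, so such caregivers may simply leave the study. Whether they are imputed or dropped is not stated. The claim about complete subjects being active caregivers is also confined to weeks 1 and 2; at 3, 6 and 12 months complete subjects include bereaved ones.

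**Conclusion.** The point holds for the error bars. As written, the rule understates standard errors and raises type I error of a path coefficient in every scenario tried: about 6-8% at 10% missing and 10-14% at 25% missing, against a nominal 5%, for n = 200. This rests on a single imputation analysed as observed, on scores missing at random in the simulations, and on assumed missing rates. R-squared inflation is conditional on how the prediction is done. The bereavement problem is conditional on Aim 1 keeping caregivers bereaved before the visit, which the text leaves open. It should be fixed before analysis: the defect touches the main hypothesis, but its size may be small if little is missing.

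**What to change.** Replace the sentence in Data Analysis with full-information maximum likelihood for the path model and a likelihood-based mixed model for Aim 3. Alternatively, use multiple imputation that carries between-imputation variance and includes bereavement status and date of death in the imputation model.

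For Aim 1, do not impute week-1 or week-2 scores for caregivers bereaved before that visit. Define the Aim 1 population as caregivers still active at the visit, report how many are excluded, and bring Purpose, Specific Aim #1, Data Collection and Data Analysis into line with that definition.

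The cost is revised wording, a suitable software module, a little more analysis work and slightly larger standard errors. Aim 1 conclusions would then apply to caregivers still active at each visit. If the effect is the f² = 0.15 that reproduces the stated 98, power remains ample even with a quarter of the scores missing.

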### Specific Aim #1

Hypothesis #1.1 (testing of the model) will be tested with path analysis modeling. Path Analysis is a multivariate statistical technique in which a series of multiple regression models are used to test the strength of the influence, and by implication, the causal relationships between variables. Change scores will be calculated by post intervention minus baseline scores. Variables will be assessed for multi-co linearity and association. Those variables that are significantly correlated with the outcome variables will be entered into the path analysis model. Possible mediator variables such as Palliative Performance Scale (PPS) and significantly correlated caregiver demographics will be co-variants. Path Analysis will be used to test the model at 1 and 2 weeks.

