### Purpose

The overall purpose of this time series mixed method study is the further development and testing of the LWHP by:

a) Determining the mechanisms of the LWHP by testing the LWHP conceptual model (Figure 1), in which 2 variables (self-efficacy and loss/grief) are hypothesized as intermediary variables for changes in hope and subsequently quality of life among rural women caring for persons with advanced cancer. We hypothesize that the administration of the LWHP will improve self-efficacy and decrease feelings of loss/grief. This will lead to a positive influence on the proximal outcome of hope and the distal outcome of quality of life. The functional status of the care recipient is hypothesized to have a moderating effect on all outcome variables. Understanding the change mechanisms or processes associated with interventions is an important step in their refinement and provides insight into the development of state of the art psychosocial interventions [15].

b) Exploring the longitudinal effects of the LWHP on hope, quality of life and health services utilization among rural women caring for persons with advanced cancer. This study is unique, as it will follow caregivers over a one-year period. The team will explore if the LWHP has benefits beyond what was found in the completed pilot study (1 and 2 weeks) by: a) comparing baseline scores of hope and quality of life to scores after the LWHP over time (3, 6 and 12 months) and b) comparing the number of physician visits and prescriptions one year prior to one year post LWHP. Approximately 50% of study subjects will become bereaved one month after study enrolment; rather than dropping bereaved caregivers from the study, the team believes these subjects will add to the understanding of hope, quality of life and health care utilization among caregivers. Thus these subjects will be retained if possible and followed through bereavement. In this way patterns of hope, quality of life and health care services utilization will be delineated over time for active and bereaved caregivers.

Justification for Focus on Rural Women:

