### Specific Aim #1

To determine the mechanisms of the LWHP by testing the LWHP conceptual model (Figure 1), by examining if, at 1 and 2 weeks post LWHP compared to baseline, self-efficacy [General Self-Efficacy Scale (GSE)] and Loss and Grief [Revised Grief Inventory (RGEI) or NonDeath RGEI (NDRGEI)] scores predict changes in hope [Herth Hope Index (HHI) Factor 1] and quality of life [SF12 V2 mental health sub score-MHS (MHS-SF12)] scores for rural women caring for persons with advanced cancer.

1.1 Main Hypothesis: The subjects' general self efficacy and loss and grief (RGEI/NDRGEI) scores will significantly predict the HHI (Factor 1) score and the mental health score on the SF12 V2 at 1 and 2 weeks.

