### Intervention: Living with Hope Program

The LWHP is theory based, focuses on the caregivers themselves and has been pilot tested. The LWHP consists of the Living with Hope film featuring caregivers of patients with advanced cancer describing their hope and a hope activity "Stories of the Present." Following viewing of the film with trained research assistants (RAs), (without discussion) the RA's instruct the subjects to take 5 minutes at the end of the day and write about their thoughts, challenges and what gave them hope over a 2 week time period. Subjects can choose to use a journal, a computer or audiotape their journals. Dosage of the LWHP is being determined by the number of journal entries and the amount of time spent on the journal. From the pilot study, compliance over a 2 week time period was 79% for number of journals and 100% for expected time. The issue of dosage and compliance is monitored in this study as it is unknown if it has an impact on the study outcomes. Variation of the dosage is expected and will be accepted in this study as this is the reality of clinical practice [10]. The 2 week length of time journaling is based on a review of journaling studies and older adults which suggests that the optimum length of time for journals is between 1 and 2 weeks [30]. We recognize that subjects may wish to continue journaling past 2 weeks if they find it beneficial. Although studies have described the benefits of journaling, the effect of the length of time journaling as a variable affecting outcome has not been supported [31]. However, it is a variable that will be monitored for its effect throughout this proposed study. If there is a significant relationship with any of the variables it will be added to the statistical analysis of conceptual framework. The possibility of co-interventions occurring such as counseling and support programs will also be monitored.

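### The path model admits only variables that already correlate significantly with the outcomes, so a hypothesised mediator can be dropped without an estimate and weak paths that pass are overstated

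*Protocol article*

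**What the plan says.** The model is set by theory. The Purpose section describes a model "in which 2 variables (self-efficacy and loss/grief) are hypothesized as intermediary variables for changes in hope and subsequently quality of life". The main hypothesis (Specific Aims and Hypotheses, hypothesis 1.1) reads: "The subjects' general self efficacy and loss and grief (RGEI/NDRGEI) scores will significantly predict the HHI (Factor 1) score", and it adds the SF12 mental health score, at 1 and 2 weeks. The Sample Size paragraph is built on the same variables: "for a power of 0.80, and an alpha of 0.05, a regression equation, including 6 variables", giving 98 subjects, later doubled to 200.

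The analysis text for Specific Aim #1 then lets the data choose: "Those variables that are significantly correlated with the outcome variables will be entered into the path analysis model". The sentence after it gives the Palliative Performance Scale (PPS) and correlated demographics their own rule as covariates, so the quoted sentence is naturally read as covering the model variables. The threshold is common to everything: "Statistical significance for all analyses will be set at p < .05".

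Two further data-driven entries are described. For demographics, Data Analysis says: "If there are significant correlations they will be added to the model". For the length of time journaling, the Intervention section says: "If there is a significant relationship with any of the variables it will be added to the statistical analysis of conceptual framework". These triggers are looser than the outcome screen, since they refer to a relationship with other variables or with any variable.

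**The concern.** Aim 1 asks whether named mediators carry the programme's effect. That calls for an estimate and an interval for each hypothesised path, whatever its size. Under the stated rule a mediator is estimated only if its simple correlation with the outcome is significant in the same data. One that fails leaves the model, and the remaining paths are then estimated without it.

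Two things are at stake. A real path that is weak, or hidden by the correlation between self-efficacy and grief, can disappear without a figure attached. A weak path that passes does so because its sample value happened to be large, so the reported coefficient is too big and its interval can be too optimistic. The Methods/Design section says that theory and programme will be revised if the model is not supported. That decision is better made on interval estimates for all paths than on which variables survived a screen.

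**Working it through.** **Inputs from the article.** Entry by significant correlation; p < .05 throughout (sidedness not stated, two-sided assumed); six variables, power 0.80, alpha 0.05; N = 98 required and 200 planned.

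**Assumptions.** True correlations of 0.10 to 0.30, because the article states none. The analysed N after attrition is unknown, so results are given at 98 and 200.

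**1. The plan's own figure.** For the overall test in multiple regression, the noncentrality is f² × N with k and N − k − 1 degrees of freedom. With k = 6 and f² = 0.15 (assumed; no effect size is stated), the smallest N with power 0.80 is 98 (power 0.804). With k = 5 it is 92, and with k = 7 it is 103. So 98 reproduces, and it belongs to a six-variable equation fitted whole.

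**2. Size of correlation needed to enter.** r_c = t / √(N − 2 + t²).
- N = 98: 1.985 / √(96 + 3.940) = 0.199.
- N = 200: 1.972 / √(198 + 3.889) = 0.139.

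A variable with true correlation 0.10 can therefore enter only by showing at least 0.199 or 0.139 in absolute value.

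**3. Chance of entry.** By Fisher's z, P(enter) ≈ 1 − Φ[(atanh r_c − atanh r)√(N − 3)], plus a very small opposite tail.
- r = 0.10, N = 98: (0.2013 − 0.1003) × 9.747 = 0.984, giving 0.163 + 0.002, about 16%.
- r = 0.10, N = 200: (0.1397 − 0.1003) × 14.036 = 0.553, giving about 29%. Simulation runs gave 29 to 30%.
- r = 0.15: simulation leaves it out 68% of the time at N = 98 and 43% at N = 200. The formula agrees within about one point.

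**4. Estimate given entry (simulation).**

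| True r | N | Mean on entry |
|---|---|---|
| 0.10 | 98 | 0.24 |
| 0.10 | 200 | 0.18 |
| 0.20 | 200 | 0.22 |
| 0.30 | 200 | 0.30 |

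**5. Two predictors correlated −0.4, as self-efficacy and grief might be.** Each candidate is screened, and the survivors are regressed (8,000 replicates).
- True paths of ±0.10: on entry they average 0.22 in size at N = 98 with 88 to 89% interval coverage, and 0.16 at N = 200 with 94% coverage.
- True paths of ±0.15: 0.22 to 0.23 at N = 98 and 0.17 at N = 200, with coverage about 95% and 97%.
- True paths of ±0.20: 0.235 at N = 98 and 0.204 at N = 200.
- The unscreened model is unbiased, with coverage of about 95% throughout.

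Under-coverage is thus confined to very weak, null or masked paths.

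**6. A masked path.** With true paths 0.30 and 0.12 and predictor correlation −0.4, the second simple correlation is 0.12 − 0.4 × 0.30 = 0. That variable enters only 5% of the time, and when it does its interval covers the truth 54% (N = 98) or 44% (N = 200) of the time. At N = 200 the first path is then estimated as 0.26 instead of 0.30. Fitted whole, the model recovers both. With the signs the theory expects and a negative correlation, self-efficacy and grief would reinforce each other. Masking therefore needs a departure from that pattern, such as a path of the unexpected sign.

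**7. False positives.** With no true effects, the rate per path, counted whether or not the variable enters, is 0.032 to 0.058 with the screen and 0.044 to 0.059 without it.

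**The case against.** Several points on the other side stand.

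- A reader might infer that the screen manufactures false paths. It does not, path by path (step 7). The chance of at least one false path is also the same with or without it: at an assumed N of 150, 0.396 against 0.387 with ten null candidates, and 0.226 against 0.228 with five. That rate comes from testing many paths at .05. A null variable that has entered will usually be significant again, but this only restates that it passed the same test. The overall F test of a screened equation does behave differently: with two null candidates a model forms in 9.2% of studies and is then almost always significant. Hypothesis 1.1 concerns individual predictors, so the point does not rest on this.
- A reader might also infer that the theory can no longer be contradicted. That goes too far. A mediator that fails the screen is itself some evidence against hypothesis 1.1, and nothing says that failures will go unreported. What is lost is the estimate and interval.
- Nothing here shows that 98 is wrong or that 200 is too few.
- For paths of 0.20 or more at the planned 200, the bias is small.
- The study is developmental, and measuring journaling time after baseline is no fault in itself, since the mediators are measured then too.
- Figure 1 is not available, so the comparison is with the model as described in the text.

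The authors may have meant the screen for additional candidates only. The text does not say so, and no other section exempts the mediators.

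**Conclusion.** The point holds in limited form. A stated rule for the main hypothesis lets a simple-correlation screen remove mediators that theory and the sample-size equation place in the model, and it inflates weak paths that survive. Under the assumed true values, a correlation of 0.10 enters between about 16% (N = 98) and 30% (N = 200) of the time and is then reported at roughly 2.4 to 1.8 times its size. A correlation of 0.15 is lost 68% to 43% of the time. The harm fades for stronger paths at N = 200, but the article gives no expected path sizes that would place the study there. Type I error per path is not affected.

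**What to change.** Replace the entry rule with a model fixed in advance:

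- Keep self-efficacy, loss/grief, hope (HHI Factor 1) and the SF12 mental health score in the model whatever their simple correlations.
- Keep PPS in the moderating role that the Purpose section hypothesises. The Aim 1 analysis text currently calls it a possible mediator and a covariate.
- State whether physician visits and prescriptions, which the sample-size equation counts but hypothesis 1.1 does not mention, belong to the model at 1 and 2 weeks.
- Name the covariates beforehand on substantive grounds.
- Report every hypothesised path with its confidence interval, including null ones.
- Label any analysis that adds demographics or journaling time after a correlation screen as exploratory.

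The cost is a change of wording and a few degrees of freedom for variables kept although not significant. No extra subjects follow from it: the six-variable calculation still gives 98 (at the assumed f² of 0.15), against 200 planned.
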